#### Dissemination

The results of the trial will be shared with the scientific community through presentations at national and international conferences. The findings will also be published in scientific papers submitted to relevant academic journals. Additionally, results will be communicated to trial participants. The implications of the results will be discussed with health care professionals and other stakeholders at clinical conferences. Furthermore, the findings will be presented to the public through meetings with interest groups and to the wider public at local meetings or seminars.

#### Compensation Details

Participants will not receive financial compensation. However, transportation expenses will be reimbursed, and meals will be provided on assessment days to ensure participant comfort and minimize any financial burden associated with participation.

## Results

Funding was secured in October and November 2022. The first participant was enrolled in May 2024. Figure 2 provides a flow diagram of the trial. As of February 2025 (initial manuscript submission), 34 participants had been enrolled, increasing to 97 participants as of December 2025. Completion of enrollment is expected in April 2026. Data analysis is expected to begin in October 2026 following the final 6-month follow-up assessment. Results are anticipated in December 2026 and will be disseminated at international conferences and through peer-reviewed publications by summer 2027.

**Figure 2. F2:**
[figure not shown]
Flow diagram of the STEPS (Social Cognitive Training Enhancing Pro-Functional Skills) trial. TAU: treatment as usual; VRSCT: virtual reality-based social cognitive training.

## Discussion

### Anticipated Findings and Implications

Autistic adults constitute a growing and largely overlooked population, for whom few clinical and research resources have been allocated. Due to the limited evidence on effective interventions for autistic adults, no national clinical guidelines have been developed for psychological interventions aimed at this population in Denmark. Sparse evidence from profunctional studies conducted in England or Sweden is often referenced when attempting to guide psychological treatment approaches for this group [86]. To our knowledge, STEPS is the hitherto largest randomized clinical trial globally investigating the effect of VRSCT for autistic adults. The results of this innovative intervention approach may significantly advance research in the field of autism. If the VRSCT intervention in the STEPS trial proves effective, it has the potential to improve psychosocial functioning and quality of life, co-occurring clinical symptoms, and reduce social cognitive deficits in autistic adults. The intervention was co-developed in collaboration with autistic adults to ensure relevance and alignment with neuro-affirming principles. It is tailored to each participant’s goals, sensory needs, and communication preferences and aims to enhance comfort, confidence, and agency in social situations that participants themselves identify as meaningful. Rather than imposing neurotypical norms of interaction, the approach supports self-defined outcomes and promotes the transfer of skills into everyday life in ways that respect and value neurodivergent ways of relating. Establishing evidence-based interventions is essential to address the debilitating psychosocial challenges encountered by this population, especially considering the absence of established gold-standard interventions. Enhancing profunctional psychosocial skills can significantly impact the lives of these individuals by enabling them to build more meaningful and intimate relationships, better maintain personal and professional relations, and improve educational and occupational functioning. Developing effective interventions for autistic adults can further contribute to filling the critical gap in available support and thereby contribute to alleviating the personal and social consequences and the economic impact associated with autism. If proven effective, the manualized VRSCT intervention from this study could be implemented in mental health services across Denmark and potentially on an international scale, supported by training and ongoing supervision. Additionally, the intervention could be adapted to fit the needs of other clinical populations experiencing social cognitive deficits, such as autistic adolescents, individuals with bipolar disorder, or individuals with psychosis [87]. This could help address the increasing demand for novel, effective interventions for psychiatric conditions globally.

### Limitations

In this trial, eligibility was based on a clinical diagnosis of autism according to *ICD-10* criteria. Although widely used in clinical and research settings, the diagnostic criteria in *ICD-10* and *DSM-5-TR* have been criticized for overemphasizing observable behaviors and reflecting a prototypical male presentation of autism. These limitations can obscure how autism manifests differently across sex and age and may overlook how traits are masked by compensatory strategies, potentially contributing to the underdiagnosis of autism in females and the delayed identification of autism in adults [41,88]. While this may also affect the representativeness of the study sample by leading to fewer females being included, the final sex distribution will help determine the extent to which this concern is reflected in the sample.

The participants in the comparison group will receive TAU, administered across multiple sites. It is expected that there will be variations in the content and duration of TAU among participants. Although the specific details of TAU for each participant will be documented at the end of the trial, this variability remains a limitation. The inconsistency in TAU introduces less control compared to an active control uniformly administered in the same setting as the experimental intervention. However, TAU was chosen as the comparator because it reflects current clinical practice available for autistic adults in Denmark. Additionally, there is no established “gold standard” intervention specifically targeting social cognitive deficits in autistic adults, which otherwise could have been an obvious choice of comparator. Further, given the absence of a “gold standard” comparator and the choice of TAU as the control condition, it is important to note that the immersive and novel nature of the VR intervention may contribute to increased participant expectancy in the intervention group compared with TAU, which does not involve comparable technology. While a sham or low-dose VR control condition was considered to address this technology-expectancy bias, it was not feasible within the scope and resources of this study. To mitigate this risk, we included both a blinded, performance-based outcome measure (HiSoC) and an informant-rated version of the Social Responsiveness Scale (SRS-2AI) as secondary outcomes. This approach allows for triangulation across self-report, informant-report, and blinded assessment. Due to the exclusion criteria regarding autistic adults with medically untreated ADHD and autistic adults with intellectual disability, the results from this trial may not be generalizable to these populations. However, the findings may still provide useful indications of the potential effects for autistic adults with ADHD, and the intervention could eventually be adapted for autistic adults with intellectual disability. Finally, as the present trial does not include follow-up assessment beyond 6 months, the absence of longer-term follow-up (eg, at 12 months) limits conclusions regarding sustained effects. As the effects of VR-based interventions may diminish over time, and follow-up assessments beyond 3 months are often lacking [89], future trials should address this.

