### Trial Design

STEPS (Social Cognitive Training Enhancing Pro-Functional Skills) is a randomized, assessor-blinded, parallel-group superiority clinical trial. A total of 140 participants will be allocated to receive either VRSCT+TAU or TAU alone. Assessments will be carried out at baseline, at cessation of intervention (3 months post baseline), and at 6 months post baseline. A flow diagram of the trial is presented in the Results section. A stratified block randomization with a concealed randomization sequence will be conducted with a 1:1 allocation. Independent assessors, blinded to the treatment, will evaluate outcomes. The analysis of outcomes will be carried out according to the intention-to-treat principle [36].

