#### Intervention Description

Participants in the experimental group will receive 12 weekly, 1-hour sessions of VRSCT, with the primary aim of enhancing psychosocial functioning and social cognition through exposure to social environments in VR. Figure 1 displays an example of the VRSCT in STEPS.

Relatives are invited to participate in the intervention. Participation of relatives is dependent on the participant’s consent. Relatives will participate in 1 session at the beginning of the intervention to add information to the assessment of the participants’ challenges. Relatives will also participate in 1 session at the end of the intervention to support transfer to everyday life. If participants decline involvement of relatives, this will be registered, and the intervention will consist of 10 individual sessions. This 12-session format is in line with previous positive findings of other short-term interventions (10‐14 sessions) targeting social cognition in autistic adults [46,47].

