#### Blinding

Following the allocation to one of the interventions, the outcome assessors will be blinded to the participants’ group assignment. Due to the nature of the intervention in the experimental group (VRSCT), participants, therapists conducting the intervention, and the clinicians managing TAU will not be blinded to the received interventions. Participants will be instructed prior to follow-up assessments not to disclose their allocation to the outcome assessors. To maintain blinding, assessments and interventions will be conducted at separate locations, ensuring that the assessors remain unaware of group assignment. Assessors will be instructed to notify their supervisors immediately if they believe blinding has been broken. If unblinding of the outcome assessor occurs, another outcome assessor blind to the allocation of intervention will conduct the subsequent assessments.

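### SRS-2AI is offered as mitigation of expectancy bias, but its informants are not blinded and, in the experimental arm only, may have attended therapy sessions

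*Protocol article*

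**What the plan says.** The Limitations section accepts that the novelty of VR may create more expectancy in the experimental arm than treatment as usual (TAU) does, and that a sham or low-dose VR control was not feasible. Its answer is that "we included both a blinded, performance-based outcome measure (HiSoC) and an informant-rated version of the Social Responsiveness Scale (SRS-2AI) as secondary outcomes", and it adds: "This approach allows for triangulation across self-report, informant-report, and blinded assessment".

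The Intervention Description says of the VRSCT arm: "Relatives are invited to participate in the intervention". There are two such contacts. "Relatives will participate in 1 session at the beginning of the intervention", to help describe the participant's difficulties. Then: "Relatives will also participate in 1 session at the end of the intervention to support transfer to everyday life". Attendance depends on the participant's consent: "If participants decline involvement of relatives, this will be registered, and the intervention will consist of 10 individual sessions". The Comparison Group section describes no similar contact for relatives under TAU.

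On blinding, Trial Design says: "Independent assessors, blinded to the treatment, will evaluate outcomes". The Blinding section says that "participants, therapists conducting the intervention, and the clinicians managing TAU will not be blinded to the received interventions". It asks participants not to reveal their allocation to outcome assessors and does not mention informants. The Secondary Outcomes section says that SRS-2AI rests on an informant's observation but not who that informant is. Table 1 schedules it at baseline, 3 months and 6 months.

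**The concern.** A second rater helps against expectancy bias only if that rater's scores do not carry the same bias. An informant who knows the allocation, has helped to describe the problems and has joined a closing session on transfer to daily life may expect improvement much as the participant does. With 12 weekly sessions and follow-up at 3 months, that closing session would fall close to the first post-baseline rating. No matching contact exists under TAU, so any resulting shift would differ by arm and would point the same way as expectancy in the primary outcome.

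What is at stake is interpretation. If SRS-2A and SRS-2AI both favour VRSCT, the Limitations text invites the reader to take the second as support for the first, although shared expectancy could produce both. The section does not list this among the trial's limitations.

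**Working it through.** **1. The plan's own figure.** Inputs from Sample Size and Power Calculation: d = 0.5, two-sided alpha 0.05, power 80%, 10% dropout.

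- Normal approximation: n per arm = 2 × (1.960 + 0.842)² / 0.5² = 62.8, so 63 (power 0.801). The exact t-test needs 64 and gives 0.795 at 63, which is close enough.
- Dropout: 126 / (1 − 0.10) = 140.

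Both stated figures reproduce, and this point changes neither.

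**2. Which outcomes the blinding covers.** Of the primary and the five secondary outcomes:

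- SRS-2A, SIAS and EQ are self-report by unblinded participants.
- SRS-2AI is informant report, with no blinding provision.
- ERT is a computerised performance test, neither self-rated nor informant-rated.
- HiSoC is recorded and scored by blinded assessors, as are the exploratory PSP and SSPA (Assessment and Collection of Outcomes).

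**3. Whether informant and attending relative are kept apart.** Relatives may attend in one arm only (Intervention Description). The informant is not identified (Secondary Outcomes). Informants are absent from the Blinding section. Refusal of relatives' involvement is registered, but the article mentions no record of whether the informant attended. Overlap is therefore possible and unprevented. It is not shown to occur in any given share of participants.

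**4. Size, by assumption only.** Let a share s of experimental-arm informants rate b SD more favourably, with no true effect and no shift under TAU. The mean difference is d = s × b. With 63 per arm, df = 124 and the noncentrality is d × √(63/2) = d × 5.612. Rejection probabilities come from the noncentral t at two-sided 5%:

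| s | b (SD) | d | Noncentrality | Two-sided rejection | Rejection favouring VRSCT |
|---|---|---|---|---|---|
| 0.25 | 0.2 | 0.050 | 0.281 | 0.059 | 0.046 |
| 0.25 | 0.3 | 0.075 | 0.421 | 0.070 | 0.062 |
| 0.50 | 0.2 | 0.100 | 0.561 | 0.086 | 0.080 |
| 0.50 | 0.3 | 0.150 | 0.842 | 0.133 | 0.130 |
| 0.75 | 0.2 | 0.150 | 0.842 | 0.133 | 0.130 |
| 0.75 | 0.3 | 0.225 | 1.263 | 0.240 | 0.240 |
| 1.00 | 0.2 | 0.200 | 1.122 | 0.200 | 0.199 |
| 1.00 | 0.3 | 0.300 | 1.684 | 0.386 | 0.386 |

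The nominal values are 0.05 two-sided and 0.025 in favour of VRSCT. The SD is held at 1. Mixing shifted and unshifted informants adds variance s(1 − s)b², for example 0.5 × 0.5 × 0.3² = 0.0225, which is negligible. The calculation is an unadjusted t-test, not the planned ANCOVA.

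**The case against.** The strongest reply is that the protocol does not contradict itself. It never calls SRS-2AI blinded, it attaches that word to HiSoC alone, and it lists informant report apart from blinded assessment. It claims to mitigate expectancy, not to remove it, and its Conclusion asks readers to interpret the results with expectancy in mind. A rater other than the participant can still be a partial check. Informant selection is also the kind of detail that a condensed article may leave to the full protocol. All of this stands, and it limits the point to the weight that SRS-2AI is given as mitigation.

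A reader might infer more in three ways:

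- **That SRS-2AI as a whole is exposed to the intervention.** The documents do not support this. The informant is never identified, attendance is optional, and a version without relatives is provided for.
- **That a false signal on SRS-2AI is as likely as 20% to 39%.** That range needs every experimental-arm informant to be shifted by 0.2 to 0.3 SD. The documents support neither the share nor the shift.
- **That the primary analysis is undermined.** The primary test and sample size do not depend on SRS-2AI, and the blinded HiSoC remains as a check.

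What the reply does not remove is the claim of mitigation itself. It is made without a caveat about informants, while the intervention invites relatives into sessions in one arm only.

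**Conclusion.** The concern holds in a limited form and is of moderate importance. SRS-2AI lacks the independence from expectancy that its stated role requires, because some experimental-arm informants may know the allocation and have taken part in the intervention. Agreement between SRS-2A and SRS-2AI should not be presented as independent corroboration.

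The size is unknown. Under the assumptions shown, false rejection on SRS-2AI runs from near nominal (about 6%) to about 24% under partial exposure, with 20% to 39% as the case in which every experimental-arm informant is shifted. These figures illustrate the mechanism and do not estimate what will happen in this trial.

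**What to change.** 1. **Wording.** In Limitations, rest the mitigation of expectancy bias on the blinded HiSoC. State that SRS-2AI, like SRS-2A, SIAS and EQ, is not blinded and may share that bias. In Trial Design, qualify the statement about blinded evaluation so that it covers assessor-rated measures only.
2. **Data and reporting.** Record the informant's identity or relationship to the participant and whether they attended VRSCT sessions. Keep the same informant from baseline to follow-up. Report SRS-2AI by informant attendance descriptively only, because attendance arises after randomisation and exists in one arm.

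Three further steps may look attractive but are not advised. Setting attending relatives' ratings to missing and imputing them would lean on a self-selected group in one arm, whose informants may also know the allocation. Moving to a non-attending informant now would change the rater between baseline and follow-up for participants already enrolled (97 of 140 by December 2025). A rule that reads an SRS-2A benefit without a HiSoC effect as expectancy would ignore that the two measure different things, everyday impairment and performance on a standardised task, and can diverge for other reasons.

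The cost is a few sentences and a small addition to the data record, part of which exists because refusal of relatives' involvement is already registered. For participants already followed up, attendance would have to be filled in from existing records where these allow. The price is a slightly weaker supporting claim for the primary result. Analysis is not expected to start before October 2026, so the change can still be made beforehand.

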### Conclusion

Autistic adults constitute a growing and largely overlooked population with limited evidence-based interventions available. To our knowledge, STEPS is the largest randomized clinical trial globally investigating the effect of VRSCT for autistic adults. If proven effective, VRSCT has the potential to improve psychosocial functioning and quality of life and reduce co-occurring clinical symptoms and social cognitive deficits in autistic adults, thereby potentially contributing to filling the critical gap in available support. The results of the trial should be interpreted in light of key limitations, including heterogeneity in TAU, potential technology-related expectancy effects, and follow-up limited to 6 months.

In light of these considerations, the findings of the trial are expected to advance research in the field of autism and may inform future clinical practice and subsequent trials, including in other clinical populations experiencing social cognitive challenges.
